## Abstract

**Background:**

Pathologies of the long head of the biceps (LHB) tendon are frequently seen as concomitant pathologies during arthroscopic surgery for rotator cuff injuries or the labroligamentous complex of the shoulder. Currently, there are two treatment options: Tenotomy is quick and easy to perform with low complications rates, but has limited functional results, especially in demanding patients; tenodesis of the tendon has shown beneficial cosmetic and functional results, but usually requires an implant for tendon-to-bone attachment and, therefore, carries the risk of implant-related complications. The implant-free loop tenodesis (LT) procedure was developed to combine the advantages of both treatment modalities and has shown promising functional and cosmetic results in a prospective pilot study. This study aims to establish the implant-free LT procedure versus arthroscopic anchor tenodesis (AAT) for the treatment of LHB pathologies during shoulder arthroscopy in terms of structural and functional outcome.

**Methods:**

A national multi-center, two-arm, parallel-group, randomized, controlled, non-inferiority trial will be conducted. Patients are eligible for trial participation if they are at least 18 years of age and present to one of the five enrolling centers with LHB tendon-associated complaints and MRI-confirmed LHB tendinopathy, instability due to SLAP or pulley lesions, or partial rupture. Patients with current or previous shoulder injury that would interfere with post-treatment rehabilitation or study assessment will be excluded from study participation. Participating patients will be randomized 1:1 to receive either LT or AAT and will be followed up for 24 months after surgery. The primary endpoint will be the functional and cosmetic outcome as assessed by the biceps-specific LHB score at 12 months after surgery. Secondary outcomes include assessment of surgery-related complications, overall shoulder and arm function, and structural outcome as evaluated by ultrasound and an additional MRI scan at the final study visit.

**Discussion:**

The study will evaluate whether the implant-free loop tenodesis procedure is non-inferior to arthroscopic implant-based tenodesis in terms of functional and cosmetic results at 12 months post-treatment.

**Trial registration:**

Trial was prospectively registered at the German Clinical Trials Register (DRKS) on 12^th^ June 2024, Registration-ID DRKS00034361, https://drks.de/search/de/trial/DRKS00034361.

## Administrative information

Note: the numbers in curly brackets in this protocol refer to SPIRIT checklist item numbers. The order of the items has been modified to group similar items (see http://www.equator-network.org/reporting-guidelines/spirit-2013-statement-defining-standard-protocol-items-for-clinical-trials/).

## Introduction

### Background and rationale 

In the adult patient population, shoulder pain is commonly associated with pathologies of the long head of biceps (LHB) tendon [1]. While shoulder arthroscopy is the fourth most common procedure performed by orthopedic surgeons in the United States [2], up to 75% of these surgical procedures are associated with concomitant pathologies of the LHB tendon [3], which should be treated concomitantly to avoid revision surgery [4]. Besides, the number of arthroscopic LHB tenodesis procedures has steadily increased over the past decade as the field of indications has widened [5].

The benefits of tenodesis versus tenotomy for the treatment of the long head of the biceps tendon have been investigated in the past. A systematic review and meta-analysis that analyzed only RCTs and prospective cohort studies showed a threefold increased risk of Popeye deformity after arthroscopic tenotomy versus tenodesis [6]. Moreover, worse functional outcomes and a higher risk of cramping pain were observed after tenotomy [6]. The functional advantages and decreased rates of Popeye deformity after tenodesis compared to tenotomy have been confirmed in several meta-analyses [7, 8], but these analyses only included studies in which LHB pathologies were treated concomitantly with rotator cuff repair, which is a much more common setting than single treatment of the LHB tendon. Therefore, tenodesis is currently considered the gold standard for treating LHB tendon disorders. However, there are numerous tenodesis techniques that differ in the way the LHB tendon is reattached to bone or soft tissue and the location of reattachment. When comparing arthroscopic suprapectoral tenodesis procedures to open subpectoral techniques, systematic reviews and meta-analyses have reported a higher complication rate for open subpectoral tenodesis [9], although both treatments showed no significant difference in functional outcomes [9, 10]. Additionally, implant-associated complications have been reported regardless of the fixation location, including implant failure [11], increased rates of wound and implant infection [12, 13], and implant irritation [14]. These complications have contributed to a higher revision rate for implant-based LHB tenodesis compared to soft-tissue tenodesis [12].

As an implant-free alternative, the “loop tenodesis” technique [15] has shown encouraging results in preliminary studies [16, 17] and is, therefore, already gaining popularity among international shoulder surgeons. The technique was introduced in 2019 and was driven by the idea of applying an easy and quick to perform technique without the need for an implant and providing stable fixation comparable to standard tenodesis techniques [15]. The principle of the technique is to create a tendon loop at the tendon stump after tenotomy (hence the term “loop tenodesis”). This loop prevents the proximal tendon from slipping through the bicipital groove upon release. As a result, the tendon loop autotenodeses in the surrounding tissue within the bicipital groove through scar formation. After a successful biomechanical study proving significantly higher stability compared to tenotomy [16], loop tenodesis was implemented in a prospective cohort pilot study that showed good short-term improvement in biceps and overall shoulder function [17]. Nevertheless, a high-evidence study directly comparing the new implant-free loop tenodesis procedure with the current standard of implant-based tenodesis technique has been missing so far.

### Objectives 

The objective of the presented study is to compare the implant-free loop tenodesis technique (experimental intervention) with the arthroscopic implant-based suprapectoral tenodesis technique (standard-of-care intervention) in a randomized, controlled, and patient- and outcome-assessor-blinded trial. The aim is to investigate the non-inferiority of the implant-free loop tenodesis technique in terms of the primary endpoint of functional outcome (LHB score) at 12 postoperative months.

Additionally, the safety of both procedures will be investigated as an additional outcome parameter of primary concern. Secondary endpoints will be functional (LHB score, Constant score, ASES score, DASH score, and SF-36) and structural outcome of the tenodesis procedures over a two-year follow-up.

### Trial design

The trial is designed as a multi-center, randomized, controlled, patient- and outcome-assessor-blinded, non-inferiority clinical trial with 1:1 allocation to two parallel groups. The total follow-up period will be 24 months after surgery. Participation in the trial is voluntary, and patients may withdraw their informed consent at any time without compromising their high-quality care. The protocol conforms to the Standard Protocol Items: Recommendations for Interventional Trials (SPIRIT) guideline.

## Methods: participants, interventions and outcomes

### Study setting

The trial will be conducted at five German medical centers with high expertise in shoulder surgery. All investigators are shoulder surgeons certified by the German, Austrian, and Swiss Society for Shoulder and Elbow Surgery (DVSE) and renowned experts in the field. In preparation of the trial, participating centers had to provide the average number of potentially eligible patients using hospital data management systems and ICD-10 codes of the included pathologies (M75.2, M75.6, S43.4, S46.1, S46.2) over the past 5 years to ensure access to the relevant target population and site capability. Capability of recruitment and recruitment progress by predefined milestones will be independently monitored by a CRO for all centers. All investigators and observers at each study site were trained in ICH-GCP E6 (R2) guidelines prior to study initiation.

The following centers met the selection criteria and have agreed to participate in the conduct of the trial: Department of Trauma Surgery, University Hospital Regensburg; Center for Musculoskeletal Surgery, Charité Berlin; Department of Shoulder Surgery, Vivantes Auguste-Viktoria-Clinic Berlin; Department of Trauma Surgery, Hand Surgery and Sports Medicine, St. Vincentius Clinic Karlsruhe; Sporthopeadicum Regensburg/Straubing.

#### Trial flow

One hundred ninety-two patients (*n* = 96 for experimental group, *n* = 96 for standard-of-care group) with LHB tendon disorders meeting all eligibility criteria will be randomized equally to implant-free loop tenodesis or arthroscopic epiosseous anchor tenodesis of the LHB tendon. The overall trial flow and timeline for data collection is outlined in Fig. 1.

**Fig. 1 Fig1:**
[figure not shown]
Trial flow of LOOPTEN randomized controlled trial

### Eligibility criteria 

Patients presenting at one of the recruiting centers will be considered for study inclusion, if they:Are at least 18 years of age at the time of presentation,Are able to speak and read German in order to understand the information given and be able to complete the study paperwork,Give written informed consent,Present with at least one of the following pathologies of the long head of the biceps tendon that are considered the most common indications for biceps tenodesis according to Creech et al. [18]:partial or subtotal tears of the LHB tendon,chronic LHB tendon inflammation,LHB tendon instability (pulley lesions),traumatic or degenerative lesions of the LHB tendon insertion at the superior labrum (SLAP lesion).

To ensure unrestricted implementation of the postoperative follow-up treatment, allow for adequate assessment during study visits, and guarantee unbiased study data, patients presenting with at least one of the following conditions will have to be excluded:osteoarthritis of the affected or contralateral shouldershoulder stiffnesschronic glenohumeral instability(previous) distal biceps tendon lesions(previous) surgery on the contralateral shoulderconcomitant fracture of the shoulders/armsconcomitant neurovascular injury of the affected shoulder/armuse of oral corticosteroidsage under 18 years or other reasons for lacking capability to consent.

### Obtaining informed consent

Patients presenting to the emergency department or outpatient clinic at any of the trial sites who show one of the included LHB tendon pathologies in MRI images will be assessed for eligibility. Patients who meet all eligibility criteria will be informed of the trial by the enrolling center’s investigators (LOOPTEN collaborators) and will receive written patient participation information. They will be given sufficient time to consider their decision. If consent to participate in the study has been obtained, a baseline assessment including epidemiologic patient data and baseline scores of all outcome parameters is scheduled (see Fig. 1 and Table 1).

**Table 1 Tab1:** Timeline and overview of schedule of enrolment, interven﻿tions and assessments of LOOPTEN

	STUDY PERIOD						
	Pre-allocation		Allocation	Post-allocation			
TIMEPOINT	Patient screening	Study inclusion	Day 0	*6 weeks **(± 7 days)*	*6 months **(± 14 days)*	*12 months **(± 30 days)*	*24 months **(±30 days)*
ENROLMENT:							
Eligibility screen	X						
Informed consent		X					
Baseline data		X					
Allocation			X				
INTERVENTIONS:							
* Study Intervention (Implant-free loop tenodesis or Implant-based arthroscopic anchor tenodesis)*			X				
ASSESSMENTS:							
* LHB score*		X		X^a^	X	X	X
* Constant-Murley-score*		X		X^a^	X	X	X
* ASES score*		X		X	X	X	X
* DASH score*		X		X	X	X	X
* SF-36 questionnaire*		X		X	X	X	X
* Adverse events of special interest*			X	X	X	X	X
* Strength measurements*		X			X	X	X
* Ultrasound examination*		X		X	X	X	X
* MRI scan*	X^b^						X

^a^Strength measurements that are included in the CMS and ASES score are omitted at the 6-week follow-up

^b^Preoperative MRI is not a study-specific examination but is part of the clinical routine and is necessary to identify the pathologies of the LHB tendon and to enroll patients in the study

### Additional consent provisions for collection and use of participant data and biological specimens 

Not applicable since additional collection and use of participant data and biological specimens in ancillary studies is not planned.

## Interventions

### Intervention description 

Both surgical and perioperative treatment will be conducted by the enrolling center. The patient is placed in a standard position for arthroscopic surgery of the shoulder. After preparation of the surgical field using standard procedures in accordance with current recommendations [19], the required standard arthroscopic portals are created. Since both the experimental intervention and the control intervention can be performed using the same skin incisions, blinding of the patients to the treatment received is possible. The surgical procedure starts with diagnostic arthroscopy to confirm structural lesions of the LHB complex and concomitant pathologies. After diagnostic arthroscopy is finished, the randomized trial intervention of implant-free loop tenodesis (experimental intervention) or implant-based epiosseous anchor tenodesis (control intervention) is performed, regardless of the concomitant pathologies.

The study groups differ in the details on how the LHB tendon is reattached to a less stress-exposed area at the humeral head after the tendon is cut at its origin. While the control treatment uses an implant for secure fixation, the trial intervention does not require an implant:

*Experimental Intervention Group: Loop tenodesis technique*
First, the intended position for tendon fixation at the entrance to the bicipital groove is debrided to create a slightly bleeding surface for improved tendon ingrowth. The LHB tendon is then securely grasped with a surgical clamp and cut close to its base. Afterwards, the tendon stump is pulled extracorporeally. About 5–15 mm of the injured proximal tenotomized tendon is then resected. The tendon “loop” is created extracorporeally by folding and doubling the proximal 1.5 cm of the LHB tendon stump in order to increase the proximal diameter of the tendon. The loop is fixed with a suture. After completion of the loop, the tendon is released and pushed intraarticularly. The tendon loop then locks into place at the previously debrided entrance to the bicipital groove, where it should gradually grow in.
*Standard of Care Intervention Group: Arthroscopic epiosseous anchor tenodesis technique*
At first, the LHB tendon is fixed in the joint with a clamp to prevent retraction after cutting. Subsequently, the LHB is cut close to its origin using arthroscopic electrocautery. Next, the LHB tendon stump is pulled extracorporeally by the clamp. The diseased proximal part (5–15 mm) is then resected, and the tendon is armed using a Krackow stitch technique with a non-absorbable suture material. The LHB tendon is fixed using a bioabsorbable knotless bone anchor (SwiveLock®, Arthrex, Naples, FL, USA or comparable) that is inserted into the previously prepared proximal bicipital groove according to the manufacturer’s recommendations and attaches the suture armed tendon stump to the humeral head.

Any concomitant procedures [12] are performed after completion of the tenodesis procedure, depending on the presence of additional pathologies.

The standardized postoperative rehabilitation protocol is identical for both treatment groups. The supervised physical therapy program follows the available recommendations for arthroscopic tenodesis procedures by the international specialist societies. Patients are instructed to avoid all elbow flexion and supination maneuvers against resistance for 6 weeks. After 6 weeks, lightweight (500 g) active elbow flexion exercises are started. Intensified physical therapy (≥ 2x/week) is scheduled from week 7 to 12 with a gradual increase in load. Sports-specific training can be started after 12 weeks at the earliest, depending on individual mobility and coordination. Modifications of the postoperative rehabilitation protocol may be required depending on concomitant procedures.

### Explanation for the choice of comparators

Among the common techniques, the *arthroscopic suprapectoral epiosseous (onlay) implant-based tenodesis technique* is considered an appropriate comparator for the following reasons:Since suprapectoral anchor tenodesis can be performed arthroscopically using the same standard arthroscopic portals that are also needed to perform the experimental intervention, the only difference from the experimental treatment will be the mode of tendon attachment (implant-based vs. implant-free), and implant-dependent outcome effects can be investigated without confounding factors such as additional skin incisions that would be needed for subpectoral tenodesis. The literature suggests that subpectoral tenodesis could carry a higher rate of perioperative surgical site infections [9].Moreover, an additional skin incision for subpectoral biceps tenodesis would preclude blinding of the study patients. An additional wound would allow patients to recognize the treatment they had received.The structural outcome of loop tenodesis should only be compared to techniques with comparable anchorage sites. In loop tenodesis, the tendon loop is positioned and later blocks itself at the entrance to the bicipital groove in a position comparable to arthroscopic anchor placement in the control group.Since intraosseous tendon-to-bone-attachment with interference screws has been shown to have increased rates of Popeye deformity [20], only epiosseous techniques are considered appropriate as a control group.

### Criteria for discontinuing or modifying allocated interventions 

Not applicable since the allocated study interventions are completed by a one-stage surgical intervention.

### Strategies to improve adherence to intervention (standardized surgical treatment)

To ensure comparable and high-quality treatments across all centers, we plan to standardize surgical treatment by:Pre-study surgeon training: Surgical techniques for both the experimental and the control interventions are already routinely performed at all participating centers. Nevertheless, educational visits of the principal investigators are planned at all centers to agree on the details of the surgical techniques using a published detailed step-by-step description and an instructional video [15] and to establish a common standard for both the surgical procedure and the standardized implementation of the examination methods to be carried out during the follow-up visits.Documentation requirements: For appropriate documentation during the surgical procedures, a protocol has to be filled in that includes the study patient’s pseudonym, the tenodesis technique, the intraoperatively apparent LHB tendon pathology, the amount of proximal biceps tendon resection, and, if applicable, the implant used. Moreover, a standardized intraoperative image of the key step of each procedure should be taken and archived locally for each surgical intervention performed on study patients.

To standardize the assessments of outcomes, evaluation of the functional outcome as part of the clinical assessment will be done only by instructed and trained examiners to avoid high inter-rater variability. Strength measurements during follow-up visits will have to be performed with the same measuring devices at each study center.

### Relevant concomitant care permitted or prohibited during the trial 

The following additional treatments are permissible in the context of this study:Surgical treatments: If the LHB tendon is surgically treated as a primary indication, surgery is in most cases supported by auxiliary procedures [12] such as repair, augmentation, or debridement of the rotator cuff, subacromial debridement with/without distal clavicle resection, and labroligamentous procedures. These procedures are thus permissible in the context of the study, especially since the primary outcome parameter (LHB score) is highly specific for LHB-related symptoms and is not affected by these additional surgical procedures.Pain medication and other concomitant medication: all standard non-opioid (NSAR, metamizole, paracetamol) and opioid (oxycodone, hydromorphone, etc.) pain medication in demand-dependent dosing is permitted as there is no significant difference between these drugs in postoperative pain levels for soft tissue injuries in recent literature [21]. Since pain medication can usually be discontinued after at least 3 postoperative months, analgesics are not expected to have a significant effect on the primary endpoint of the study after 12 postoperative months. The use of corticosteroid drugs [22, 23] or fluoroquinolone antibiotics [24] is known to adversely affect tendon metabolism and healing and increase the risk of injury. The use of these active substances is permitted during the study period but must be precisely documented. Moreover, all other concomitant medication is permitted during study participation since no effect of any medication on the primary endpoint of the study is expected.Rehabilitation: Physical therapy is conducted postoperatively according to the standardized rehabilitation plan, which was designed in accordance with the recommendations of international specialist societies and approved in preparation for this trial by the German, Austrian, and Swiss Society for Shoulder and Elbow Surgery (DVSE) and our Loop Tenodesis Patient Committee. Depending on the performance of any additional procedure, modifications of the postoperative rehabilitation protocol may be required that include a prolonged resumption of exercise.

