### Sample size calculation 

The primary objective of this study is to show the non-inferiority of loop tenodesis in comparison with arthroscopic anchor tenodesis with respect to the primary clinical outcome LHB score (scale range 0–100). The clinical non-inferiority margin was set at 5 points on the LHB score, which was based on statistical considerations and clinical judgment. Moreover, an expert panel of German-speaking shoulder surgeons was consulted on the study design and the choice of non-inferiority margin. The panel defined a non-inferiority margin of 5 points, taking into account the differences in LHB scores between the established procedures and the minimal clinically important differences in other related scores. For loop tenodesis to be considered standard of care and to show non-inferiority to implant-based tenodesis techniques, it has to outperform the technically easier procedure of biceps tenotomy. According to Kerschbaum et al. [26, 34], the mean LHB score of patients treated with biceps tenotomy is at least 5 points lower than that of patients treated with arthroscopic epiosseous suprapectoral anchor tenodesis. Setting the non-inferiority margin at 5 points can also be considered a benchmark for outperforming biceps tenotomy as a historical control, as suggested by studies by Kerschbaum et al. [26, 34]. Moreover, according to the literature [17, 25–28], we expect a mean LHB score of 85 with a standard deviation of 10 for both treatment groups at 12 months. The non-inferiority margin of 5 points is half of the expected standard deviation, which is widely accepted as the minimal clinically relevant difference of PROs [35]. To show non-inferiority with a non-inferiority margin of 5 points and a standard deviation of 10 points with a power of 90% at a one-sided 2.5% level of significance, a total of *n* = 172 patients are required for statistical analyses. Assuming an early drop-out rate of 10% (change of indication during arthroscopy and thus no need for surgery or no information on the clinical outcome (drop-out before week 6)), a total of *n* = 192 patients (96 per group) need to be randomized. Sample size was calculated by using SAS 9.4 and the procedure proc power.

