The 2^nd^ estimand is based on the composite policy strategy. The endpoint is the LHB total score > 80 points at 12 months after surgery as a binary endpoint. Intercurrent events as defined above will be classified as non-responders regardless of the LHB score at month 12. The summary measure will be the difference in the proportions between the two treatment arms.

The 3^rd^ estimand is based on the hypothetical policy strategy. The endpoint and the summary measure are defined according to the primary estimand, but for all patients with intercurrent events, the LHB score at month 12 will be replaced by a hypothetical score. This score is based on a multiple imputation method as for the primary estimand, using only information before the occurrence of the intercurrent event. All estimands together will provide a good answer to the question of whether the new method of loop tenodesis is non-inferior or even superior to the standard anchor tenodesis procedure. Furthermore, subgroup analyses based on age and sex will be performed. Statistical analyses of the secondary endpoints will be carried out in an exploratory manner without any multiplicity adjustments as described in detail in the Statistical Analysis Plan. Descriptive safety analyses will be provided.

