
Thus, the two techniques investigated in this trial differ in the way in which the LHB tendon is attached to the humeral bone (implant-based vs. implant-free) and is secured against slippage through the bicipital groove. By participating in the current trial, patients receive blinded treatment for LHB tendon pathologies. Although the experimental treatment group will be treated with a new surgical technique with little data available, we expect a high willingness to participate in the study because the details of the tenodesis technique usually play a subordinate role in patient perception and both the control intervention and the experimental intervention are already routinely performed surgical techniques in daily practice. Nevertheless, the recruitment plan requires patients to be enrolled regardless of concomitant pathologies and concomitant arthroscopic procedures. This is unavoidable because isolated pathology of the LHB tendon without accompanying shoulder pathologies accounts for only 5% of cases and is, therefore, a rarity in everyday clinical practice [44]. The sole inclusion of patients with isolated pathologies of the long biceps tendon would therefore not only question the feasibility of the recruitment target based on the sample size calculation, but would also not represent the reality of clinical practice. To overcome the limitation of heterogeneity of the study population and selection bias of the results, the biceps-specific LHB score was chosen as a primary outcome parameter for this trial. The score was introduced in 2011 [25] in order to provide a useful tool for the highly specific evaluation of the LHB tendon after surgery, because the most established shoulder scores only incompletely cover LHB tendon disorders and mainly depend on the results of concomitant procedures. The LHB score has proven to be a valuable tool for evaluating outcome after LHB tenotomy and tenodesis procedures in previous studies [17, 25–30].

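### The protocol asserts that concomitant shoulder procedures leave the LHB score unaffected, and names no stratum, model term or subgroup that would allow for the opposite

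*Protocol article*

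**What the plan says.** Under Relevant concomitant care, the protocol allows rotator cuff repair, augmentation or debridement, subacromial debridement and labroligamentous procedures. Part of its reason is that the primary score "is highly specific for LHB-related symptoms and is not affected by these additional surgical procedures". It says such procedures accompany LHB surgery in most cases and gives no percentage.

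Other sections bear on that statement:

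- **Primary outcome measure:** the LHB score combines patient-reported symptoms (pain, cramps or tenderness), Popeye deformity and flexion strength, each compared with the other side.
- **Intervention description:** "Modifications of the postoperative rehabilitation protocol may be required depending on concomitant procedures". The concomitant care section adds that this can mean a later return to exercise.
- **Discussion:** "isolated pathology of the LHB tendon without accompanying shoulder pathologies accounts for only 5% of cases". The choice of a biceps-specific score is the answer offered to the resulting heterogeneity.
- **Allocation:** randomisation is stratified by center only.
- **Statistical methods:** the primary model contains treatment, center and baseline LHB score. On subgroups: "Furthermore, subgroup analyses based on age and sex will be performed".

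**The concern.** An absolute statement about the primary endpoint is made without direct support, and the protocol's own description of the score makes it doubtful. Pain around the shoulder and flexion strength are quantities that a cuff or labral procedure, or a later return to exercise, could plausibly move. If they do, there are two separate consequences.

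- **A shift equal in both arms** (a prognostic effect) adds variance that the primary model does not remove. This costs power and makes non-inferiority harder to show.
- **A different treatment effect** in patients with and without cuff pathology (effect modification) would be averaged into one overall difference. None of the analyses named in the protocol would display it, and readers could carry the overall result over to a patient group in which it is not known to hold.

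**Working it through.** **Inputs from Sample size calculation and Trial design.** "The clinical non-inferiority margin was set at 5 points on the LHB score"; "we expect a mean LHB score of 85 with a standard deviation of 10 for both treatment groups at 12 months"; "with a power of 90% at a one-sided 2.5% level of significance"; "non-inferiority clinical trial with 1:1 allocation to two parallel groups".

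**Step 1. The plan's own figure.** The normal approximation gives n per arm = 2 × (1.960 + 1.282)² × 10² / 5² = 84.1, so 85 per arm (170). The t-based calculation gives 86 per arm, 172 in total, with power 90.3%. Then 172 / 0.90 = 191.1, which rounds up to 192 in two equal arms. Both stated figures, 172 and 192, are reproduced.

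**Step 2. What the 5% measures.** It is the share with isolated LHB *pathology*. So about 95% have an accompanying pathology. The share with an accompanying *procedure* is not given, and nor is the share whose rehabilitation is changed.

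**Step 3. Cost if the effect is the same in both arms.** Suppose a share p of patients differs from the rest by d points, with SD 10 within each group. Then SD = √(10² + p(1 − p)d²). Both p and d are assumptions.

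| p | d | SD | Power with 86 per arm |
|---|---|---|---|
| – | 0 | 10.0 | 90% |
| 0.30 | 5 | 10.3 | 89% |
| 0.30 | 10 | 11.0 | 84% |
| 0.50 | 10 | 11.2 | 83% |

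A fixed factor in the model would remove this added variance. The table may overstate the loss. The planning SD cites, among other sources, the pilot study, which the Discussion says used the same eligibility criteria, so the SD of 10 may already reflect a mixed population. Baseline LHB score in the model may also absorb part of it.

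**Step 4. What could go unseen if the treatment effect differs.** Assume that loop tenodesis has a 6-point deficit in a share f of patients and none in the others. The overall deficit is D = 6f, SE = 10 × √(2/86) = 1.525, and P(declare non-inferiority) = Φ((5 − D)/1.525 − 1.96).

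| f | D | P(declare non-inferiority) |
|---|---|---|
| 0.05 | 0.3 | 87% |
| 0.20 | 1.2 | 70% |
| 0.30 | 1.8 | 56% |
| 0.40 | 2.4 | 40% |

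Every D here lies inside the 5-point margin. These are therefore not false conclusions about the whole population. They show only that the overall test can pass while one group has a deficit beyond the margin. Neither the 6 points nor f comes from the documents.

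**Step 5. What a subgroup report can deliver.** Take a stratum of 30% of 172, or 25.8 per arm. The 95% half-width is 1.96 × 10 × √(2/25.8) = 5.5 points, wider than the margin. The SE of the interaction is 10 × √(2/25.8 + 2/60.2) = 3.3, so a 6-point interaction would be detected with probability Φ(6/3.33 − 1.96) = 44%. Under true equality the stratum alone would show non-inferiority with probability Φ(5/2.78 − 1.96) = 43%.

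**The case against.** The case on the other side is strong on several points.

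- **The mixed population is the target.** The primary estimand covers randomised patients as enrolled, and the Discussion argues that isolated cases would not reflect practice. Averaging over concomitant pathology is then what is wanted. This stands.
- **The arms are protected alike.** Allocation is random, the tenodesis is done regardless of concomitant pathology and before the other procedures, and the rehabilitation plan is the same in both arms. Concomitant surgery is therefore not a confounder. This stands.
- **The score was chosen for its specificity.** The Discussion gives that rationale and cites earlier studies. Those sources are not available here, so whether the score is affected cannot be settled. This supports a qualified statement, but not an absolute one.
- **The SAP may add covariates or subgroups.** It may, and a short subgroup list is not in itself an error. But the protocol does fix the primary model, and it offers the specificity of the score as the answer to heterogeneity. The imputation model lists other injuries as a baseline predictor. That term is ambiguous, and it does not enter the primary model.

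A reader might infer something stronger: that about 95% of patients have surgery which shelters the loop while it heals, so that non-inferiority would be declared from patients in whom the techniques are barely tested. The documents do not support this. The 95% counts pathologies. Changes to rehabilitation are described only as possible, without share or duration. All patients avoid resisted elbow flexion and supination for 6 weeks. Nothing says that the changes protect the tenodesis.

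**Conclusion.** The point holds as a should-fix on wording and analysis. The claim that the score is unaffected is stated more firmly than the document supports, and no analysis named in the protocol allows for its being wrong. The size of any effect is unknown. Under the assumed shifts in Step 3, power falls from 90% to between 89% and 83%, and possibly less than that if the planning SD already covers mixed patients. Effect modification by cuff status would go unseen in the named analyses, but the documents give no evidence that it exists. The overall non-inferiority conclusion for the mixed population is not invalidated, and the scenario probabilities in Step 4 should not be read as error rates.

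**What to change.** 1. In Relevant concomitant care, delete the statement that the score is unaffected, or soften it to an expectation with its supporting sources.
2. Add rotator cuff tear on the preoperative MRI (yes/no) as a fixed factor in the primary model.
3. Add the same factor to age and sex as a pre-specified descriptive subgroup, giving the treatment difference with its confidence interval in each stratum and the interaction. Rest no separate non-inferiority claim on a stratum; Step 5 shows why.
4. Do not use procedures performed as the factor. They follow allocation, and the surgeon is not among those blinded. The drop-out allowance for a change of indication during arthroscopy also implies that patients are randomised before the arthroscopic findings are known. The MRI belongs to screening in Table 1, and concomitant diagnoses are collected at baseline, so the factor is available before randomisation.

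The cost is protocol and SAP wording, one coded variable from an existing scan and one more model term, with no extra visit or patient. The limits are an imprecise subgroup estimate (about ±5.5 points for an assumed 30% stratum) and a factor that captures cuff pathology but not labral lesions.
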